## Abstract

**Background:**

Pesticide poisoning and unsafe handling among pesticide users, particularly with farmers, pose a significant threat to both public health and the environment. Despite efforts to improve farmers Knowledge, Attitude and Practices, most interventions lack tailored education and sustained follow-up, limiting their effectiveness. This trial assesses the impact of need-based educational intervention with educational documentary, improving safe pesticide practices among farmers in Karnataka, India.

**Methods:**

The study is a multicentric randomized controlled trial, which will be conducted across 4 phases in Udupi, Mysuru, and Shivamogga districts of Karnataka. Phase 1 features a cross-sectional study design of 175 farmers to evaluate their baseline knowledge, attitudes, and practices on usage of pesticides. Phase 2 employs semi-structured interviews with 20–30 farmers and 10–20 key stakeholders, including pesticide dealers, scientists from Farm Science Centers [Krishi Vigyan Kendra (KVK)], and joint directors of agriculture to explore pesticide handling approaches, challenges, and community-specific needs while handling pesticides. The findings from Phases 1 and 2 will help in development and validation of an intervention in the form of educational video in Phase 3 which will be piloted. Phase 4 involves implementing the validated intervention and conducting long-term follow-up to assess the impact and sustainability. Phase 4 will be a two-arm, single-blind, parallel-group randomized controlled trial, with villages randomized 1:1 into intervention and control groups. The intervention group will receive a 15–20-minute educational documentary in the local language, while the control group will receive no intervention. The outcomes will be evaluated based on changes in Knowledge, Attitudes, and Practices (KAP) scores, with assessments conducted immediately post intervention, at 6 months, and at 12 months from the date of intervention. These will be correlated with outcomes including quality of life and laboratory parameters.

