### Intervention

The primary component of the intervention will be a 15–20-minutes educational documentary in the local language. Topics like safe pesticide usage, proper storage, disposal methods, and associated health risks will be covered in this documentary. These elements will be presented through a story that will be displayed as a short documentary or movie among the farmers. Cluster sampling method will be utilised for selecting participants based on characteristics including age, education, and years of experience with pesticides or agriculture. The intervention will be provided in the intended villages at community centres or village halls.

The control group will not receive any educational intervention during the study period. Participation records will be maintained to track adherence to intervention, and any participant’s decision to withdraw from the study will be documented. If withdrawn, data collected up to the point of withdrawal will be retained for analysis. The appropriate reason will be documented for withdrawal if available.

To maintain the integrity of the study, participants will be requested to refrain from engaging in other pesticide-related educational initiatives, although they may continue their regular farming activities. Adherence to the intervention and pesticide practices will be monitored through regular follow-up calls, personal visits, and collaboration with field officers, community leaders, and local organizations.

The detailed participant timeline has been provided in Fig. 2, following the SPIRIT 2025 format [39] .

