### Secondary outcomes

The secondary outcomes of this trial include (i) adherence to safe pesticide handling practices, (ii) knowledge on first aid for unintentional or occupational pesticide exposure. Additional outcomes comprise (iii) frequency of direct pesticide exposure, assessed through self-reported practices and associated health hazards during follow-up, and (iv) development and dissemination of a localized educational tool, evaluated qualitatively, to promote sustainable knowledge and practices. These outcomes have been selected for their clinical relevance in addressing the short- and long-term health risks associated with indiscriminate pesticide usage, enhancing overall safety, and fostering effective behavioural change among farmers. These outcomes will be assessed by an investigator through observation of the practices and using the self-reported checklists.

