### Participant timeline

The trial will be conducted over a period of 3 years in 4 phases. During the phase 1, with duration of 8 months, 175 farmers will be recruited to assess their baseline knowledge, attitudes, and practices (KAP) regarding pesticide usage, which will be correlated with quality-of-life and biochemical parameters.

In the phase 2, which will last 4 months, around 20 to 30 farmers will participate in qualitative interviews to share their needs and perspectives on pesticide usage patterns, disposal methods, and storage practices. Additionally, 10 to 20 key stakeholders, including pesticide dealers, scientists from Farm Science Centre [Krishi Vigyan Kendra’s (KVK’s)], joint directors of agriculture, assistant director of agriculture, subject matter specialist [SMS] will be involved from the selected villages across different districts, to gather qualitative insights and recommendations regarding pesticide usage patterns.

Following this, phase 3 will be conducted over 6 months, which focuses on the development and validation of the educational module. This phase will be followed by a pilot implementation lasting further 6 months.

The final phase 4 will be executed as a randomized controlled trial (RCT), where the validated educational module will be implemented in the selected villages for a specific duration of 2 months. Participants will be followed up at intervals of 6 months and 12 months. The total duration of phase 4 will be 1 year.

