## Methods: data collection, management, and analysis

### Data collection and management

In phase 1, data will be collected in person through face-to-face interactions using baseline questionnaires, including the KAP questionnaire and the SF-36 Quality of Life (QoL) questionnaire from RAND Health. Additionally, qualitative interviews will be conducted, and laboratory tests (blood samples) will be collected from enrolled participants. All quantitative data will be stored in OpenEpi version 3.1 software and later transferred to SPSS version 20.0 (IBM, New York, NY, USA) for statistical analysis.

In phase 2, qualitative interviews will be recorded with prior consent, transcribed, and stored securely on a password-protected device. These recordings will be transcribed and translated to verbatim, and themes and sub-themes will be developed using NVivo software for qualitative analysis.

In phase 3, after developing the educational documentary, its validation will be conducted using a Likert scale (ranging from 1 to 4) and face-to-face focus group discussions (FGDs). These discussions will be recorded, transcribed, translated, and analysed to extract themes and suggestions, which will be incorporated to refine the documentary.

In phase 4, pre- and post-intervention questionnaires will be administered to both the intervention and control groups, mirroring the data collection process from Phase 1. The collected data will be stored in OpenEpi version 3.1 software and subsequently analysed using SPSS version 20.0 (IBM, New York, NY, USA).

Throughout the study, participant identities will remain anonymized, and all data will be coded for confidentiality. At the conclusion of the study, data will be discarded as per study protocols. Missing data, such as those resulting from loss to follow-up or participant withdrawal, will be documented with appropriate justifications and reported in the results.

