### Statistical analysis

All data collected through the KAP and QoL questionnaires will be entered into SPSS version 20.0 (IBM, New York, NY, USA) for statistical analysis. Paired t-tests will be performed for continuous variables to compare pre- and post-intervention results. For improvements in quality of life and changes in laboratory parameters, the Wilcoxon Signed Ranks Test will be used. The results from the KAP surveys will be presented as mean ± standard deviation (SD). Qualitative interview data will be analysed using NVivo software, with thematic analysis to identify key patterns, insights and to understand the needs and perception of the farmers. Subgroup analyses based on confounding factors such as age, gender, and education level will be conducted to assess differential effects of the intervention. An intention-to-treat analysis will be performed and per-protocol analysis for participants deviating from the protocol.

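### Follow-up is timed from an intervention date that control villages lack, and effects are judged by pre-post change, so a 6-month change in practice, exposure or laboratory values can reflect spraying conditions rather than the film

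*Protocol article*

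**What the plan says.** The Abstract (Methods) sets Phase 4 assessments "with assessments conducted immediately post intervention, at 6 months, and at 12 months from the date of intervention". The Participant timeline section repeats the intervals without a starting point: "Participants will be followed up at intervals of 6 months and 12 months". The Primary outcomes section speaks only of baseline, post-intervention and periodic follow-up measurements.

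The Intervention section states: "The control group will not receive any educational intervention during the study period". Controls are nevertheless measured: under Data collection and management, "pre- and post-intervention questionnaires will be administered to both the intervention and control groups".

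Delivery is "implemented in the selected villages for a specific duration of 2 months", and "The total duration of phase 4 will be 1 year" (both Participant timeline).

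The Secondary outcomes include "frequency of direct pesticide exposure, assessed through self-reported practices and associated health hazards during follow-up", and that section adds that an investigator observes practices and uses self-reported checklists. Laboratory parameters appear in the Abstract and in the Statistical analysis section.

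On analysis, the Statistical analysis section says: "Paired t-tests will be performed for continuous variables to compare pre- and post-intervention results". Quality of life and laboratory changes get the Wilcoxon signed-rank test, which is also paired. No test between the arms is named. The Primary outcomes section likewise describes mean changes over time.

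**The concern.** A visit rule counted from the intervention date cannot be applied to the arm that has none. The visible text does not say when a control village's follow-up clock starts, or that its visits fall at the same time of year as those in intervention villages.

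This matters for outcomes that depend on whether farmers are currently spraying: exposure frequency, practices an investigator can observe, and blood values. The Background links pesticide demand to climatic variation, to a subtropical climate that favours insect breeding, and to rainfed as well as irrigated land. Variation within the year is therefore plausible. If baseline falls in heavy spraying and the 6-month visit in light spraying, exposure drops without any help from the film. With the opposite timing, a real benefit could be hidden. A paired pre-post test cannot separate the two.

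**Working it through.** The plan states no figure on this point, so there is nothing to reproduce. Three checks follow.

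**1. Timeline (figures from the Participant timeline section).** The phases sum to 8 + 4 + 6 + 6 + 12 = 36 months, which matches the stated 3 years. If delivery is spread over the 2 months, the last village's 12-month visit falls at month 2 + 12 = 14 of Phase 4, against a stated length of 1 year. The total would then be 8 + 4 + 6 + 6 + 14 = 38 months. The rule counted from the intervention date and the stated Phase 4 length need reconciling on that reading.

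**2. How far apart in season two visits can be (assumed yearly cycle with one peak, amplitude A).** The largest difference between visits L months apart is 2A·|sin(πL/12)|:

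- L = 1: 0.52A
- L = 2: 1.0A
- L = 6: 2.0A
- L = 12: 0

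So the 6-month change is the most exposed. The 12-month visit returns to the season of a baseline taken just before the film. Arms seen 2 months apart could differ by up to 1.0A. With two peaks a year the formula becomes 2A·|sin(πL/6)|: the 6-month difference is 0, but a 2-month gap between arms gives up to 2A·sin 60° = 1.73A. The direction of the problem therefore depends on a crop calendar that the document does not give.

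**3. False-positive rate of a paired test within one arm when the film has no effect.** Assumptions, none of them given in the document: within-person correlation r = 0.5; n = 30, 60 or 87 farmers per arm; seasonal shift s in SD units; independent farmers; normal approximation. The standard error of the mean change is √(2(1 − r)/n), the standardised shift is λ = s/SE, and the rejection rate is 1 − Φ(1.96 − λ) + Φ(−1.96 − λ).

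Example: n = 60, s = 0.25. SE = √(1/60) = 0.129; λ = 0.25/0.129 = 1.94; rejection rate = 49.1%.

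| Shift s | n = 30 | n = 60 | n = 87 |
|---|---|---|---|
| 0 | 5% | 5% | 5% |
| 0.1 SD | 8.5% | 12.1% | 15.4% |
| 0.25 SD | 27.8% | 49.1% | 64.5% |
| 0.5 SD | 78.2% | 97.2% | 99.7% |

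The signed-rank test is also a within-arm comparison and is open to the same shift; it was not computed separately. Under the same simplifications, comparing the change between arms on matched dates removes a shift common to both arms and keeps the rate at 5%. That requires similar crops and seasons in the two arms.

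**The case against.** The strongest reply is that a concurrent randomised control arm already deals with season: a shift shared by both arms cancels. That is correct, and timing alone does not create confounding. But the cancellation needs two things that the text does not provide: visits at the same calendar time and a comparison between arms. The superiority framework in the Trial design section suggests that such a comparison is intended, yet the tests named are paired.

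Other points also stand:

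- The document has no data on spraying within the year, and eligibility requires regular spraying.
- The 2-month delivery period need not mean staggered villages, so a 2-month gap between arms is a worst case.
- Self-reported checklists give some information even when there is no spraying to observe.
- Crop varieties and spraying techniques are stratification variables. That helps balance but does not fix visit dates.
- The participant timeline figure is not shown, and an article may leave its visit calendar to the full protocol. The lack of a season rule is therefore weaker evidence than the starting point that the Abstract does state.

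A reader might infer that all trial results, including knowledge, attitude and the 12-month visit, are confounded with season. The document does not support that. Knowledge and attitude have no shown seasonal mechanism, and 12 months is largely season-matched to baseline. A reader might also infer a definite bias of known size; any such size would be assumed.

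**Conclusion.** The point holds in a limited form. The stated follow-up clock cannot be applied to control villages, and the stated tests would read any seasonal change between baseline and 6 months as a change due to the film. The outcomes at risk are exposure frequency, observed practice and laboratory values at 6 months. Whether bias occurs, and how large it is, depends on within-year variation in spraying, which is plausible but not quantified. Over assumed shifts of 0 to 0.5 SD, the paired test's false-positive rate runs from 5% to 78% with 30 farmers per arm and from 5% to nearly 100% with 87. This should be settled before Phase 4 starts, because visit dates cannot be realigned afterwards.

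**What to change.** 1. Reconcile the unit of allocation first. The Recruitment section randomises districts; the Abstract and the randomisation section randomise villages. Pairing within a district is possible only if villages are the unit. If districts are allocated, common dates may not fully cancel season, because crops and spraying calendars can differ between districts.
2. Give each control village an index date paired with that of an intervention village, within district and with similar crops where villages are randomised. Hold the baseline, immediate, 6-month and 12-month visits of each pair in a common calendar window. Reconcile the 2-month delivery plus 12-month follow-up with the 1-year Phase 4.
3. At every visit, record the date of last spraying and the number of spray-days in the recall period. Record days since last spraying at the Phase 1 blood draw as well, as an adjustment variable for the correlation of KAP with biochemistry.
4. Base the effect on practice, exposure and laboratory values on the between-arm comparison at the same calendar time, not on within-arm change from baseline.
5. Keep total exposure frequency as the outcome. A rate per spraying occasion should not replace it, because that would hide a benefit if the film leads farmers to spray less often.

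The cost is protocol wording, two questions on the form and co-ordinated visit dates. No extra participants are needed. The downside is somewhat less flexible field scheduling.

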**Discussion:**

The study aims to provide robust evidence on the role of need-based educational intervention in promoting safe pesticide practices among farmers in rural region. The primary aim of the study is to develop practical strategies to enhance public health and farmer safety by addressing gaps and contextual relevance. It seeks to improve farmers’ knowledge, attitudes, and practices regarding pesticide use, ultimately enhancing their quality of life and promoting better health and safety outcomes.

**Trial registration:**

The trial is registered at Clinical trials Registry India with the trial registration number CTRI/2024/06/069678.

**Supplementary Information:**

The online version contains supplementary material available at 10.1186/s12889-026-26501-6.

## Background

India ranks among the largest pesticide users globally, with pesticide-related disorders emerging as a significant public health concern [1]. The adoption of intensive agricultural practices and reliance on synthetic pesticides has led to extensive occupational exposure, increasing the risk of severe health outcomes, including neurological disorders [2].

Around 4.19 million metric tons of pesticides were used worldwide in 2019, with China leading the consumption at approximately 1.76 million metric tons. In Southeast Asia, pesticide usage continues to rise annually, with 20% of developing countries—including Cambodia, Laos, and Vietnam—identified as major consumers [3]. India stands as a leading pesticide producer in Asia, manufacturing around 90,000 tons annually and holds 12th position in the world for manufacturing of pesticides [1].

Between 2010 and 2014, the global average cost-benefit ratio was 0.645 g of total pesticides per kilogram of crop yield. The average annual pesticide consumption during this period was 2.784 kg ha–1 worldwide, while India reported a significantly lower average of 0.26 kg ha–1 [4]. 

The WHO classifies highly toxic pesticides into categories such as Class I and Class II, including organophosphates and carbamates, which have been linked to significant health effects. These include health risks on central nervous system (CNS), skin disorders, cancer, and respiratory problems [5]. A recent systematic review with meta-analysis from 2022 [6], examined the association between pesticide exposure and allergic diseases—such as asthma, allergic rhinitis, and atopic dermatitis in children and adolescents. The findings indicated that children and adolescents exposed to pesticides had a two-fold increased risk of asthma symptoms [OR = 2.14; 95% CI: 1.26–3.64] [6].

South Asia has one of the highest pesticide usage rates globally, driven by its agricultural demands and variations in climatic conditions. Although alternatives to chemical pesticides are available, their limited efficacy has led to a greater dependence on synthetic insecticides. While these products play a crucial role in enhancing agricultural productivity, their improper and excessive use has become increasingly common, contributing to persistent health problems among farmers [7, 8].

Additionally, pesticide residues can enter households through various pathways, including contaminated clothing, ingestion, inhalation, dermal absorption, floor dust, and other take-home routes [9, 10]. A 2023 study conducted in Indonesia among a population of 105 farmers reported acute health issues associated with pesticide exposure, with 41.9% experiencing Occupational Skin Diseases [OSD] [11, 12] and 28.78% suffering from dry-eye syndrome [11, 13]. Furthermore, a 2024 meta-analysis of 38 studies involving over 118,000 children revealed a 24% increased risk of asthma and a 34% higher risk of wheezing among children exposed to pesticides [14, 15].

Long-term exposure has been frequently associated with chronic neurological disorders, including Alzheimer’s disease [16, 17], Parkinson’s disease [18, 19], cognitive impairments [3.4%], and neuropathies [61.7%] [11]. Additional neurological problems include seizures, epilepsy, and cancer [20, 21]. Children are particularly susceptible to pesticide exposure, which is linked to growth retardation, behavioural disorders, allergies, and other adverse health effects [19, 22].

Karnataka, a key agricultural state in India, encompassing a geographical area of 190,500 km² [19.05 million hectares], with 65% of its population relying on agriculture as their primary livelihood [23]. Pesticide application is a widespread practice among farmers in this state. According to the 2022–2023 annual report from the Agriculture Department of Karnataka, overall pesticide usage has slightly declined over the past decade. Nevertheless, Karnataka remains among the states with the highest per-hectare expenditure on pesticides. This reflects the intensive application of these chemicals on major crops such as paddy, ragi, maize, sorghum, red gram, Bengal gram, sunflower, groundnut, cotton, and sugarcane [24].

Karnataka state is home to 8.68 million farming families, cultivating 118,050 km² (11.81 million hectares) of rainfed and irrigated land [25]. The subtropical climate of Karnataka, which is prone to insect breeding, further increases the demand for pesticides. Despite this, the adoption rate of chemical pest control methods in Karnataka is relatively low [22%] compared to other agricultural states, highlighting a potential gap in awareness or accessibility to modern educational interventions regarding pesticide usage and its implications [26].

The increasing reliance on pesticides has led to unsafe handling, improper mixing, inadequate spraying techniques, insufficient use of personal protective equipment (PPE), and a lack of expertise, all of which pose significant health risks [27]. Although the dangers of pesticide poisoning have been addressed through various educational interventions, including seminars, pamphlets, puppet shows and lectures, the effectiveness of these efforts is often compromised by low literacy rates, limited farmer engagement, and insufficient follow-up [28].

Based on the findings of the 2021 systematic review [29], educational interventions were less successful in changing participants behaviours and lowering exposure risks, despite successfully improvement in their knowledge and attitudes. This was observed primarily because of the limited follow-ups, that lasted less than one month or six months. Furthermore, none of the studies explored the use of technological interventions [29]. The long-term sustainability among the reported study is still unclear, as evidenced by the fact that only 7 of the 21 studies [29], that were part of the evaluation concentrated on knowledge and beliefs and had follow-up periods longer than six months [29, 30].

Besides, studies utilizing need-based educational approaches are scarce, and when such studies are conducted, they frequently lack adequate follow-up, thereby limiting their effectiveness [31]. Regardless of the study design or type of intervention implemented, research consistently suggests that the effectiveness of educational programs in agricultural settings is often hindered by insufficient follow-up and a lack of context-specific customization. These limitations undermine the long-term impact and sustainability of the interventions, emphasizing the need for comprehensive strategies that include ongoing support and monitoring [29, 32].

The proposed multicentric randomized controlled trial (RCT) aims to address the challenges faced by farmers by implementing a mixed-methods approach. This study incorporates a video-based educational intervention with periodic long-term follow-ups, which enhances both the effectiveness and the sustainability of the knowledge gained by farmers. The need-based educational strategy ensures that the intervention targets specific knowledge gaps and practices, thereby improving the effectiveness and long-term adoption of safe pesticide practices.

It is hypothesized that by focusing on KAP and integrating qualitative insights from relevant stakeholders, alongside visual educational tools, the study will offer a sustainable and contextually relevant solution to the persistent issue of pesticide poisoning and its associated health impacts.

